## Abstract

**Introduction:**

Peripheral arterial disease (PAD) commonly coexists with chronic kidney disease (CKD). Patients with symptomatic PAD often require endovascular revascularisation to relieve pain or salvage limbs. However, the iodinated intra-arterial contrast routinely used in these procedures is nephrotoxic, placing patients with CKD at increased risk of acute kidney injury (AKI) and long-term renal decline. Carbon dioxide (CO_₂_) delivered via automated injection is a potential alternative imaging contrast medium. This trial will evaluate whether using CO_₂_ instead of iodinated contrast reduces the risk of AKI and short-term renal function decline in this high-risk group.

**Methods and analysis:**

This is a multicentre, open-label, prospective randomised controlled trial across six secondary-care National Health Service (NHS) vascular surgery centres. A total of 174 patients with PAD and CKD undergoing endovascular intervention will be randomised 1:1 to receive iodinated contrast (standard of care) or CO_₂_ via automated injector (Angiodroid). All perioperative care will follow local NHS protocols.

The primary outcome is log serum creatinine at 2, 30 and 90 days postprocedure. Key secondary outcomes include: incidence and severity of AKI within 48 hours postprocedure, major adverse kidney events (death, dialysis or >25% estimated glomerular filtration rate decline) by 90 days, inpatient length of stay, procedural pain, quality of life, procedural success, reinterventions, acceptability and feasibility (patient/practitioner questionnaires) of using CO_2_, and cost-effectiveness (healthcare resource use analysis). A mixed-methods process evaluation will be undertaken with patients and clinicians.

**Ethics and dissemination:**

The trial has been approved by an NHS ethical review committee (24/WA/0332) and patients have been involved in trial design. Findings will be disseminated to participants, clinicians and the wider public through patient groups, lay summaries, social media, conferences, peer-reviewed journals and NHS policy channels.

**Trial registration number:**

ISRCTN23564393.

STRENGTHS AND LIMITATIONS OF THIS STUDYThis is a multicentre, pragmatic randomised controlled trial conducted across six National Health Service (NHS) vascular centres, enhancing the generalisability of findings.The trial design incorporates both clinical and health economic analyses, allowing evaluation of effectiveness and cost-effectiveness within routine NHS care.Outcome assessments are based on objective, routinely collected biochemical measures, reducing measurement bias.A mixed-methods process evaluation enables detailed assessment of feasibility, acceptability and implementation factors for CO_₂_ angiography.The open-label design may introduce performance bias, although objective renal outcomes minimise its potential impact.

## Introduction

### Background and rationale

 When revascularising the lower limbs of people with peripheral arterial disease (PAD), iodine-based contrast medium is used to visualise arteries and allow operators to perform the procedure.^1 2^ This contrast medium, being nephrotoxic, can contribute to acute kidney injury (AKI), the most common complication after these procedures. One way to minimise AKI risk may be to use carbon dioxide (CO_2_) as a contrast medium, which is not nephrotoxic and does not contain iodine (CO_2_ is used widely in other invasive procedures, for example, laparoscopy).^3^ The value of using CO_2_ to reduce AKI in this context, however, has not been tested in a randomised setting.

AKI is the most common complication of endovascular (minimally invasive) revascularisation for PAD, especially in patients with pre-existing chronic kidney disease (CKD).^1^ Postintervention AKI in this context is strongly and independently associated with higher mortality, cardiovascular events and National Health Service (NHS) costs, in the short and long term.^4 5^ One of the key reasons why these patients develop AKI is the use of iodinated contrast medium, which is injected to visualise their arteries.^6^ CO_2_ can also be used as a contrast medium during such procedures; CO_2_ is safe to be injected intra-arterially and not nephrotoxic.^7^,^9^ The use of CO_2_, however, can be challenging due to the complexity of the procedure, imaging quality and pain during injection. Recently, automated intra-arterial CO_2_ injectors were developed. These new injectors overcome many constraints associated with injecting CO_2_ in arteries during revascularisation.^7^,^11^ This could lead to a shift in how arterial revascularisation is performed, preventing AKI and the major complications associated with it. Before this happens, the value of CO_2_ via automated injectors as a means of preventing AKI postendovascular revascularisation needs to be tested in a randomised trial. We also need to understand the acceptability, feasibility and factors that may influence the adoption/implementation of the technology in the NHS, as per National Institute for Health and Care Research (NIHR) and Medical Research Council guidance.^12^ This proposed randomised research will provide the necessary information to guide the implementation/adoption of this technology in the NHS, potentially leading to improved outcomes for patients and decreasing healthcare costs.

### Research questions

Does the use of CO_2_ via an automated injector during endovascular revascularisation reduce: (1) the likelihood of short- and medium-term renal decline? (2) The volume of iodinated contrast medium necessary to complete the procedure?What is the acceptability, feasibility and the factors that may influence the adoption of this technology in the NHS from the perspective of patients and practitioners?What are the costs of performing endovascular lower limb revascularisation using an automated CO_2_ injector, compared with the usual NHS standard of care (no use of CO_2_)?

### Objectives

#### Primary objective

Perform a multicentre prospective randomised controlled trial (RCT) to assess whether using an automated CO_2_ injector reduces the impact of endovascular revascularisation on renal function in patients with PAD and CKD by reducing the amount of nephrotoxic iodinated contrast medium necessary to complete the revascularisation.

#### Secondary objectives

Assess the acceptability, feasibility and the factors that may influence the adoption of this technology in the NHS from the perspective of patients and practitioners, record and report the overall costs of performing endovascular lower limb revascularisation using an automated CO_2_ injector versus the usual NHS standard of care.

## Methods and analysis

### Trial design

Multicentre, prospective, open-label, parallel-group RCT. The trial will also include a health economic evaluation to assess cost-effectiveness from both an NHS and a wider English societal perspective.

### Trial setting

Six NHS hospital sites in England providing arterial intervention services, which are already using the Angiodroid CO_₂_ injector. Preoperative and postoperative care will follow local protocols of care (pragmatic RCT).

### Inclusion criteria

Age >18 years.Undergoing any peripheral arterial revascularisation with an endovascular component.Estimated glomerular filtration rate (eGFR) <60 mL/min/1.73 m^2^ at baseline or known established CKD (two separate eGFR readings <60 mL/min/1.73 m² in the last 3 months).Signed informed consent.

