### Exclusion criteria

Known allergy to iodinated contrast media.Individuals already on long-term dialysis at the time of screening.An inability to understand the languages in which the trial materials are provided.

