#### Assignment of interventions and randomisation

1:1 electronic randomisation. Minimisation based on CKD stage, age, diabetes and tissue loss.

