### Data collection, management and analysis

#### Data collection methods

Clinical and patient-reported data will be collected by trained research staff at each participating NHS site, supported by the coordinating Clinical Trials Unit (CTU). Data will be collected at baseline, during the index procedure and at follow-up visits at Days 2, 30 and 90, which coincide with routine NHS care.

Baseline data will include demographics, medical history, comorbidities, height, weight and baseline SCr. Procedural data will include details of the intervention, type and volume of contrast used, pain scores using a VAS and any immediate complications.

Follow-up data will include repeat SCr measurements, assessment of adverse events (AEs), MAKE, reinterventions, hospital stay duration and patient-reported outcome measures (EQ-5D-5L and SF-36) at Day 90. Healthcare resource use will be captured via case report forms (CRFs) and participant questionnaires to inform the health economic evaluation.

Optional qualitative data will be collected via semistructured interviews with a purposive sample of participants and practitioners to explore acceptability, feasibility and implementation factors. Interviews will be conducted by trained qualitative researchers following a topic guide.

All data will be entered into a secure, validated electronic data capture system managed by the CTU. Source data verification and monitoring will be conducted according to the trial monitoring plan and Sponsor standard operating procedures (SOPs).

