#### Data analysis

The LCTU Trial Statistician will be responsible for planning, monitoring and carrying out analyses, supervised by a senior statistician. Statistical analysis will be undertaken according to a prespecified statistical analysis plan (SAP) written prior to database lock and reported following Consolidated Standards of Reporting Trials statements. The baseline characteristics of the participants will be summarised by group. Continuous variables will be summarised using mean and SD, or median and IQR if data do not have a symmetric distribution. Categorical variables will be summarised with counts and percentages. The primary analysis of the primary outcome will be carried out in the ITT population using a mixed effects model with participant as a random effect to account for repeated measures over time. Each participant will contribute up to three repeated outcome measures to the model in addition to the baseline SCr. The model will be adjusted for the stratification and minimisation variables (age, sex, baseline CKD stage and presence of tissue loss). Secondary outcomes will be analysed on a complete case population and reported similarly to the primary outcome using appropriate methodology to compare randomised groups; binary outcomes using logistic regression, continuous outcomes using linear regression or, where not normally distributed, using appropriate non-parametric methods.

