### Statistical methods

#### Planned analyses for primary and secondary outcomes

The primary analysis will be performed on an ITT basis, including all randomised participants as allocated. The primary outcome—log SCr at 2, 30 and 90 days postprocedure—will be analysed using a mixed-effects model with participant as a random effect to account for repeated measures over time. The model will adjust for baseline log SCr, stratification and minimisation factors (age, sex, baseline CKD stage and presence of tissue loss).

Secondary outcomes will be analysed using appropriate statistical methods: binary outcomes (eg, AKI incidence, MAKE) will be compared between groups using logistic regression; continuous outcomes (eg, contrast volume, QoL scores) will be analysed using linear regression, or non-parametric tests if data are not normally distributed. Time-to-event data, if applicable, will be analysed using survival analysis methods such as Kaplan-Meier estimates and Cox proportional hazards regression. All analyses will be conducted using validated statistical software according to a prespecified SAP.

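### Precision would improve at little cost if the planned procedure, fixed before randomisation, were a covariate in the creatinine and contrast-volume models

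*Protocol article*

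**What the plan says.** All references are to the protocol article.

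- *Inclusion criteria*: a patient qualifies when "Undergoing any peripheral arterial revascularisation with an endovascular component". None of the *Exclusion criteria* concerns the type or extent of the procedure.
- *Assignment of interventions and randomisation*: "Minimisation based on CKD stage, age, diabetes and tissue loss".
- *Planned analyses for primary and secondary outcomes*: "The model will adjust for baseline log SCr, stratification and minimisation factors (age, sex, baseline CKD stage and presence of tissue loss". *Data analysis* gives the same four factors. All are characteristics of the patient.
- For contrast volume, the same section says that "continuous outcomes (eg, contrast volume, QoL scores) will be analysed using linear regression, or non-parametric tests if data are not normally distributed". It names no covariate.
- *Data collection methods*: "Procedural data will include details of the intervention, type and volume of contrast used, pain scores using a VAS and any immediate complications". Procedure details are therefore collected, but no stated analysis of creatinine or contrast volume uses them.
- *Other secondary outcomes* includes the proportion of procedures carried out according to plan, taken from medical records.

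**The concern.** The eligibility wording covers a single-segment angioplasty, a multi-segment intervention and, on a plain reading, an operation with an open surgical part. The word hybrid is not in the article. The extent of the procedure plausibly affects how much contrast is needed, and may affect how creatinine changes afterwards. Baseline creatinine cannot absorb an effect that arises after baseline, and tissue loss is at best a partial stand-in for extent.

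A predictor that could be known before randomisation is therefore left in the error term. What is at stake is precision: a little on the primary outcome, and plausibly more on contrast volume. Contrast volume matters because the primary objective names reduced contrast as the mechanism, and *Key secondary outcome* says the trial is adequately powered for it.

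**Working it through.** **Inputs from *Sample size calculation*:** SD of log creatinine 0.25; correlation 0.67 among baseline and the three follow-up values; target difference 0.075; power 90%; alpha 0.05, taken as two-sided; 78 per group, and 174 in total after 10% drop-out; a 20% reduction from a median of 70 mL of contrast, which is 14 mL. No SD is given for contrast volume.

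**Reproducing the plan's figure.** For the mean of three follow-up values adjusted for one baseline value, with equal correlations:

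- Variance factor = (1 + 2 × 0.67)/3 − 0.67² = 0.3311.
- Residual variance = 0.3311 × 0.25² = 0.0207.
- n per group = 2 × (1.96 + 1.2816)² × 0.0207 / 0.075² = 77.3, so 78.
- Total 156; 156/0.90 = 173.3, so 174.

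The stated sample size is reproduced. At 78 per group the standard error is √(2 × 0.0207/78) = 0.023, and power is 0.9025.

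**Primary outcome with a procedure covariate.** If the covariate explains a share R² of the residual variance, the variance becomes 0.0207 × (1 − R²). The values of R² are assumed.

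- R² = 5%: power 0.9163 at 78 per group; 74 per group would give 90%.
- R² = 10%: power 0.9295; 70 per group.
- R² = 20%: power 0.9535; 62 per group.

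The gain is about 1 to 5 percentage points.

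**Is chance imbalance an extra harm?** Take a class with prevalence h and effect D on log creatinine. The SD of the between-arm imbalance is √(2h(1 − h)/78), and multiplying by D gives the typical shift in the estimate.

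- h = 10%, D = 0.10: 0.048 × 0.10 = 0.0048, which is 21% of the standard error.
- h = 30%, D = 0.20: 0.073 × 0.20 = 0.0147, which is 64% of the standard error.

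The shares of residual variance, h(1 − h)D²/0.0207, are 4% and 41%. These are the squares of 21% and 64%. If the planned SD includes procedure variation, the shift is already part of the planned standard error and should not be added to it.

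**Contrast volume.** For a mean difference of 14 mL at 78 per group, 90% power needs an SD of at most 14 / [(1.96 + 1.2816) × √(2/78)] = 27 mL. Power at assumed SDs, without a covariate and then with one explaining an assumed 30% of the variance:

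- SD 30 mL: 83%, then 94%.
- SD 40 mL: 59%, then 74%.
- SD 50 mL: 42%, then 55%.

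These figures treat the 14 mL as a difference in means and take the SD and R² as equal in both arms.

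**The case against.** The strongest reply is that nothing here is wrong. Every trial leaves some predictors unadjusted, randomisation keeps the test valid, and the choice of further covariates is a matter of judgement. That stands, and it is why the point is an improvement and not a correction.

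Several stronger readings are tempting but not supported:

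- *The estimate is biased, or chance imbalance is a separate harm.* Allocation is random, so there is no systematic bias. The imbalance sits inside the planned standard error, as shown above.
- *The primary outcome is underpowered.* The 78 per group reproduces. The SD comes from the team's own cohort and pilot, and may already include procedure variation.
- *Procedure type could account for as much as 41% of the residual variance.* That needs 30% hybrid operations and an effect of 0.20 averaged over three visits, which is 2.7 times the target difference (0.20/0.075). Nothing in the article supports either value.
- *The plan for the procedure is not recorded.* The baseline lists do not mention it, but they are summaries, and the outcome on procedures going to plan cannot be scored unless the plan is on record.
- *Eligibility is too wide.* The design is declared pragmatic. In "AKI is the most common complication of endovascular (minimally invasive) revascularisation for PAD" the bracketed words explain the term endovascular and restrict nothing.

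On contrast volume, the covariates of a secondary model may properly be left to the SAP, so their absence from the article is not a fault. The gain also does not carry over directly to a non-parametric test, and R² may differ between arms because CO₂ is meant to replace iodinated contrast in one of them.

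**Conclusion.** The point holds as a cheap improvement. Eligibility leaves the procedure mix open, the stated primary covariates describe the patient only, and none is named for contrast volume.

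The gain on the primary outcome is modest: from 90.25% to between 91.63% and 95.35% power if the covariate explains 5% to 20% of the residual variance. For contrast volume it is plausibly larger, for example 59% to 74% at an SD of 40 mL with 30% explained. With no SD stated, neither adequate nor inadequate power for that outcome can be confirmed; 90% holds only up to about 27 mL. The explained shares and the contrast SDs are assumptions, because the article reports no procedure mix, no procedure effect and no spread of volume.

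**What to change.** Record the planned procedure class before randomisation, for example endovascular only or hybrid, and single or multi-segment. The plan already needed to score whether the procedure went to plan can supply it. Add the class as a fixed covariate in the log-creatinine model, and make the analysis of contrast volume a regression that includes it. Use the planned class, not the performed one: allocation is open-label, so what is actually done may depend on the arm.

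The cost is up to two baseline fields, a phrase in *Data analysis* and in *Planned analyses for primary and secondary outcomes*, and one or two model terms. Eligibility, minimisation and sample size need not change. For participants already randomised, the class must come from the dated listing made before randomisation, ideally coded by someone unaware of the arm.

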### Exclusion criteria

Known allergy to iodinated contrast media.Individuals already on long-term dialysis at the time of screening.An inability to understand the languages in which the trial materials are provided.

#### Inclusion criteria for healthcare professionals involved in the parallel non-randomised implementation study

Clinicians who have performed the revascularisation procedure for the patient participants included in the RCT.

### Interventions

Participants will be randomised to either:

*Control group*: standard iodinated contrast medium used during endovascular PAD revascularisation (standard of care).*Intervention group*: CO_₂_ contrast, delivered via a dedicated injector system (Angiodroid injector) as an alternative to iodine contrast.

All other procedural aspects remain consistent across groups and as per the usual standard of care (pragmatic RCT). Those in the intervention group will be allowed the administration of standard iodine-based intra-arterial contrast if deemed necessary by the operators in order to complete the procedure safely.

### Outcomes

Outcomes and assessments are based on national and international consultation with AKI experts, our national stakeholder/patient survey, patients’ opinions during our patient involvement work and our previous/ongoing randomised and observational research relating to renal decline in vascular patients.^1^

We plan to evaluate the impact on kidney function postendovascular revascularisation in the RCT arms both in the short term (AKI) and at 90 days (medium term). We will include creatinine measurements at 2, 30 and 90 days, powered to detect a clinically meaningful difference in serum creatinine (SCr) at 90 days. These three SCr measurements will also allow us to compare AKI incidence based on the Kidney Disease Improving Global Outcomes (KDIGO) definition of AKI between groups and calculate/compare the incidence of major adverse kidney events at 90 days (MAKE outcome). This will provide novel information on the clinical value of using the proposed intervention, addressing the relevant evidence gap and leading to adoption of the intervention in the NHS, for the immediate benefit of patients in this high-risk group. We have chosen not to use AKI incidence at 2 days as the primary outcome, as it does not allow us to evaluate medium-term renal injury and would also necessitate recruitment of a prohibitively large sample of patients, without adding clinical information that would aid translation to clinical care.

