### Statistical considerations

#### Sample size calculation

174 patients (87 per group) provide 90% power to detect clinically meaningful differences. Based on our preliminary data (observational AKI study of 2021 patients with PAD/CKD treated in three sites and a pilot study on the use of CO_2_ in PAD procedures),^78 15^,^17^ we expect the SD of log SCr values at 2, 30 and 90 days to be 0.25 log (µmol/L). We assume the correlation of the baseline, 2, 30 and 90-day measures to be 0.67, which is conservative. With these assumptions, a sample size of 156 patients (78 per group) would have a 90% power to detect a mean difference of 0.075 log (µmol/L) in SCr values (effect size of 0.3) at 2, 30 and 90 days postsurgery, between intervention and control groups with an alpha value of 0.05. Allowing for a 10% drop-out, 174 will be recruited. This sample size will also allow us to assess for a 20% reduction in the volume of iodinated contrast used in those having the intervention versus control (median of 70 mL of iodinated contrast used in our published series without CO_2_). In order to ensure the population remained truly per intention-to-treat (ITT) for the primary outcome, multiple imputation will be implemented to deal with missing data in instances where participants are missing any of the SCr values. Values will be predicted using a multivariate normal regression equation with 20 imputations being used.

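### The protocol says the trial is powered for a creatinine difference at 90 days, but 78 per group gives 90% power only for the effect averaged over days 2, 30 and 90; a separate 90-day contrast has about 71%

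*Protocol article*

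**What the plan says.** The Outcomes section of the protocol article describes creatinine at 2, 30 and 90 days as "powered to detect a clinically meaningful difference in serum creatinine (SCr) at 90 days". The same section treats AKI as the short-term effect and 90 days as the medium-term one. One reason it gives for not making AKI at 2 days the primary outcome is that AKI at 2 days cannot show medium-term injury.

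The calculation is under Sample size calculation. On variability: "we expect the SD of log SCr values at 2, 30 and 90 days to be 0.25 log". On correlation: "We assume the correlation of the baseline, 2, 30 and 90-day measures to be 0.67, which is conservative". On the result: "a sample size of 156 patients (78 per group) would have a 90% power to detect" a difference of 0.075 log, "in SCr values (effect size of 0.3) at 2, 30 and 90 days postsurgery, between intervention and control groups", at alpha 0.05. Allowing for 10% drop-out, 174 are to be recruited.

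The analysis, under Planned analyses for primary and secondary outcomes, is a "mixed-effects model with participant as a random effect to account for repeated measures over time", adjusted for baseline log creatinine. The Data analysis section adds that each participant supplies up to three follow-up values. No power calculation for day 90 alone appears anywhere in the article.

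**The concern.** The Outcomes section makes a power claim about one time point, while the sample size section gives one difference for three time points. Averaging three correlated measurements reduces the variance, so a sample size that is sufficient for the average is too small for any single visit.

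The difference matters for interpretation because the 90-day horizon is part of the stated case for this endpoint. In the average, day 2 carries as much weight as day 90. Relying on the Outcomes sentence, a reader could take a significant average as proof of kidney protection at 90 days. The same reader could take a non-significant day-90 estimate as coming from a comparison with 90% power.

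**Working it through.** **Inputs, all from Sample size calculation:** SD 0.25 at each follow-up visit; difference 0.075, so standardised effect 0.075/0.25 = 0.3; correlation ρ = 0.67, read as equal between all pairs of baseline, day 2, day 30 and day 90; alpha 0.05; power 90%; 78 per group evaluable. Sidedness is not stated; two-sided is assumed because it reproduces the stated figure.

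**Formulas.** For the mean of m follow-up values adjusted for one baseline value, the variance is SD² × F, with

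F = [1 + (m − 1)ρ]/m − ρ²

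n per group = 2 × (1.960 + 1.2816)² × F / 0.3²

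power = Φ(0.3 × √(n / 2F) − 1.960)

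**Step 1: reproduce the plan's figure (m = 3).**
- F = (1 + 2 × 0.67)/3 − 0.67² = 0.7800 − 0.4489 = 0.3311
- n = 2 × 10.508 × 0.3311 / 0.09 = 77.3, so 78 per group, as stated
- Power with 78 = Φ(3.256 − 1.960) = 90.2% (89.9% with the t distribution)
- Drop-out: 156/0.9 = 173.3, so 174, as stated

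The other readings tried do not give 78:

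| Reading | n per group |
|---|---|
| 3 visits, no baseline adjustment | 183 |
| 3 visits, change from baseline | 103 |
| 3 visits, baseline-adjusted, one-sided | 64 |
| 2 visits, baseline-adjusted | 91 |
| 1 visit, baseline-adjusted | 129 |
| 1 visit, baseline-adjusted, one-sided | 105 |
| 1 visit, change from baseline | 155 |
| 1 visit, no baseline adjustment | 234 |

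**Step 2: the day-90 contrast with the same inputs (m = 1).**
- F = 1 − 0.67² = 0.5511
- Power with 78 per group = Φ(2.524 − 1.960) = 71.4% (70.8% with t)
- Power with 87 per group, if nobody is lost = Φ(2.665 − 1.960) = 76.0% (75.5% with t)
- Difference detectable with 90% power at 78 per group = 3.2416 × 0.25 × √(2 × 0.5511/78) = 0.096 log
- For 90% power at 0.075: n = 2 × 10.508 × 0.5511 / 0.09 = 128.7, so 129 per group, 258 evaluable, about 287 recruited (258/0.9)

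**Step 3: sensitivity to the baseline to day-90 correlation (F = 1 − ρ²), 78 per group.**

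| ρ | Power at day 90 |
|---|---|
| 0.60 | 65% |
| 0.67 (stated) | 71% |
| 0.70 | 75% |
| 0.75 | 81% |
| 0.80 | 88% |
| 0.85 | 94% |

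**Step 4: illustration only.** The documents give no effect pattern other than a single 0.075. Suppose the effect were 0.075, 0.050 and 0.025 at the three visits. The average would be 0.050, with 58% power for the average and 13% for day 90. Suppose instead it were 0.225 at day 2 and zero afterwards. The average would be 0.225/3 = 0.075, with the same 90% power and no 90-day effect at all.

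**The case against.** The strongest reply is that the sample size section quotes one difference for all three visits, and the described model mentions no visit-by-arm term. Read that way, the model has a single treatment coefficient. If the effect is constant, that coefficient is also the day-90 effect, and 90% power applies to it. This is a fair reading of the calculation, and it is why the 90% figure should be kept for the common effect. It does not rescue the Outcomes sentence. The constancy assumption is not stated, and the same section separates short-term from 90-day effects when it explains the choice of endpoint. A 90-day claim that relies on early and late effects being equal should say so.

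A second reply is that 0.67 is described as conservative. This also has weight: the shortfall shrinks as the correlation rises. At 0.80 with all 87 per group observed, power would reach 91% (Φ(0.3 × √(87/(2 × 0.36)) − 1.960)). But neither the higher correlation nor complete follow-up is among the planning assumptions, so the claim does not follow from the inputs given.

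A reader might also infer two stronger criticisms:
- **That the plan leaves its primary test undefined.** The exact contrast, any visit-by-arm term and the covariance structure are commonly left to the statistical analysis plan, which is not shown. Their absence from a condensed article is not a fault.
- **That type I error is inflated by testing three visits.** No section plans a separate test at each visit; the analysis is one model.

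**Conclusion.** The power claim in the Outcomes section is wrong as written. On the protocol's own inputs, 90% power belongs to the baseline-adjusted effect averaged over, or common to, the three visits. A separate day-90 contrast has about 71% power with the 156 evaluable patients and 76% if all 174 have a day-90 value. At 78 per group, 90% power at day 90 is reached only for a difference of about 0.096 log.

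These figures assume two-sided alpha 0.05, baseline adjustment and a baseline to day-90 correlation of 0.67. The 71% should not be quoted as a fixed property of the trial: at 78 per group it becomes 81% at a correlation of 0.75 and 88% at 0.80.

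It would go too far to infer that the sample size is miscalculated or the trial too small for its primary analysis. Both 156 and 174 reproduce, and the three-visit outcome is stated consistently elsewhere in the article. The error lies in what the Outcomes section says that number of patients can show.

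**What to change.** Bring the Outcomes section into line with Sample size calculation, and carry the same wording into the statistical analysis plan:

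1. State that the 90% power is for the baseline-adjusted difference in log creatinine averaged over days 2, 30 and 90, assuming the effect is the same at each visit, and name that average (common) effect as the primary contrast.
2. State the day-90 power for 0.075 log: about 71% with 78 per group, 76% with 87, at correlation 0.67; and that 90% power at 78 per group requires about 0.096 log.
3. Report the day-90 difference with its confidence interval as a named secondary estimate.
4. Do not describe a significant average as a demonstrated effect at 90 days.

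The cost is a change of wording and a less favourable published figure for day 90. The sample size stays as it is.
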